**System credibility support**					
	Trustworthiness (“A system that is viewed as trustworthy will have increased powers of persuasion”)	The system should provide information that is truthful, genuine, and unbiased.		Feedback after the self-test score and information offered in BRI are written in a noncoercive style and leave all autonomy to the user, for example, “We respect your decision, of course, but would encourage you to talk about your feelings, either with us or with someone close to you.”	
	Expertise (“A system that is viewed as incorporating expertise will have increased powers of persuasion”)	The system should provide information that conveys knowledge, experience, and competence.		The BRI was built on the results of a pilot study conducted among the users of the current self-test. The information or feedback provided has been developed by the professionals of 113 (psychologists, communication advisors, and researchers).	
	Real-world feel (“A system that highlights people or organizations behind its content or services will have more credibility”)	The system should provide information about the organization and the people behind it.		BRI includes photos and experiences from counselors telling about their work in the helpline.	
	Authority (“A system that leverages roles of authority will have enhanced powers of persuasion”)	The system should convey authority.		Self-test and BRI are in the same style and tone of voice as the helpline’s website and include the helpline’s logo. BRI includes persuasive messages about the many help seekers that contact the helpline. BRI includes persuasive messages about the expertise of the helpline and its counselors.	

^a^BRI: barrier reduction intervention.

### Tailored Information

After selecting a barrier in the barrier survey, participants receive tailored information with the purpose of addressing common concerns and misconceptions about the helpline. Tailored information is useful for giving people the right information and suitable feedback and helps with selecting the most effective persuasive strategies. To persuade people to overcome their barriers to the helpline, the principles of the PSD model as well as the principles of consistency, social proof, likability, and authority derived from Cialdini’s [24] principles of influence will be used [23].

### Statistical Analysis

The analyses will be carried out with an intention-to-treat analysis. Missing values will be imputed using the MICE package in R (v4.2.2; R Core Team 2022) [25]. In order to verify the randomization process and inspect drop-outs, independent *t* tests and chi-square tests will be used to determine whether the control group and the intervention group, as well as the completers and noncompleters, are comparable on baseline factors (ie, gender, age, SIDAS score, and in treatment or not). Chi-square analysis will also be used to test the hypothesis that participants who receive the brief BRI are more motivated to contact the suicide prevention helpline (using the direct link yes/no) than participants in the control condition. To evaluate the effectivity of the BRI in increasing service use by men and middle-aged people, and to examine potential moderators, logistic regression analysis will be used.

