### Sample Size

When assuming probabilities of 0.49 and 0.39 for contacting the helpline for the intervention group and the control group, respectively (based on Jaroszweski et al [15]), a power of .8 and alpha of .05, a sample size calculation for logistical regression analysis (2-tailed) indicates a total sample size of 775 participants [21]. We estimate that about 10% of participants drop out during the intervention; therefore, at least 853 participants have to be included. Furthermore, we estimate that approximately 30% of respondents score below the cutoff point for high risk of suicidal behavior, and based on Jaroszewski et al [15], we expect that 20% of respondents will indicate a high probability of contacting the helpline [15]. We, therefore, estimate that a minimum of 1706 respondents need to be recruited. We will continue to recruit participants until there are enough participants per condition.

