### Measures

The primary outcome measure is the use of a direct link to the helpline after completing the intervention or the control condition. Due to the anonymous nature of the helpline, it is not possible to measure if people who do not directly use the link to the helpline, contact the helpline at a later point in time. Therefore, the self-reported likelihood of contacting the helpline will be included as a proxy measurement. This will be measured by the question “How likely are you to contact 113's helpline via chat or phone?” with answering options ranging from “not likely” to “very likely” on a 5-point scale. Other measures include gender, age group, SIDAS score, being in treatment for mental health problems (yes, no, and on a waiting list), and satisfaction with the self-test (Dutch CSQ-3) [22].

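### An unrestricted imputation rule, read as written, imputes helpline-link use for people who left without using the link; leaving should count as not used

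*Protocol article*

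**What the plan says.** The Measures section states: "The primary outcome measure is the use of a direct link to the helpline after completing the intervention or the control condition". It adds that contact made later cannot be measured, and gives self-reported likelihood of contact as a separate proxy.

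The Sample Size section states: "We estimate that about 10% of participants drop out during the intervention". It raises the required number from 775 to 853 on that account.

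The Statistical Analysis section states: "The analyses will be carried out with an intention-to-treat analysis". The next sentence sets the missing-data rule: "Missing values will be imputed using the MICE package in R". The primary comparison is a chi-square test of whether participants given the barrier reduction intervention (BRI) "are more motivated to contact the suicide prevention helpline (using the direct link yes/no) than participants in the control condition".

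The article nowhere says how link use is coded for someone who leaves the session before reaching the link.

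**The concern.** Link use is an act that either happens in the session or does not. A randomised person who closes the page before the link has not used it, so the value is a known no and not an unobserved quantity. The plan expects such people, enlarges the sample on their account, keeps them in an intention-to-treat set and imputes missing values without exception. Taken together, this most naturally means that their link use is imputed.

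MICE in its usual form assumes missing at random and would give leavers roughly the link-use rate of similar people who stayed. The baseline variables in the plan (gender, age group, SIDAS score, treatment status) cannot correct for this, because leaving itself settles the outcome. The quantity estimated is then link use had everyone stayed, which is not link use among all randomised. An intervention that drives people away would not be charged for doing so, and one that keeps people in the session would get no credit for it. After randomisation the arms read different texts, so unequal drop-out is possible.

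**Working it through.** **Inputs from the protocol article.** Sample Size: link-use probabilities 0.49 (BRI) and 0.39 (control), two-sided alpha 0.05, power 0.80, total 775, drop-out about 10% with no split by arm, 853 randomised. Abstract: equal allocation. That gives 853/2 = 426.5 per arm.

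**Reproducing the plan's figure.**
- Two-proportion formula without continuity correction: n = [1.96·√(2·0.44·0.56) + 0.842·√(0.49·0.51 + 0.39·0.61)]² / 0.10² = 386 per arm, 772 in total.
- Wald formula for the log odds ratio: 388.2 per arm, 776.4 in total.

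The stated 775 is reproduced to within rounding and choice of formula. The 853 is 775 × 1.10.

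**Equal drop-out.** Assume that 0.49 and 0.39 are rates among completers. Imputation within arm under missing at random reproduces the completer rate; actual link use among all randomised is completer rate × (1 − drop-out).
- BRI: 0.49 × 0.90 = 0.441. Control: 0.39 × 0.90 = 0.351. Difference 0.090, against 0.100 after imputation (a factor of 1/0.90 = 1.11).
- Odds ratio: (0.441/0.559)/(0.351/0.649) = 1.46, against 1.50 after imputation.
- Risk ratio: 0.441/0.351 = 0.49/0.39 = 1.256 either way.
- Link uses credited that did not occur: 426.5 × 0.10 × 0.49 = 21 (BRI) and 426.5 × 0.10 × 0.39 = 17 (control).

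**Unequal drop-out.** The splits below are assumptions. True link use among all randomised is now held fixed, so imputation reproduces true rate / (1 − drop-out). Rejection rates come from simulation (427 per arm, 4000 trials, 20 imputations by arm, Rubin's rules), except the 12%/8% row, which uses a normal approximation.

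| True use, BRI/control | Drop-out, BRI/control | Rates after imputation | Difference (points) | Rejects, imputed | Rejects, leavers coded no |
|---|---|---|---|---|---|
| 39%/39% | 10%/10% | 43.3%/43.3% | 0 | 5% | 5% |
| 39%/39% | 12%/8% | 44.3%/42.4% | 1.9 | about 8% | 5% (nominal) |
| 39%/39% | 15%/5% | 45.9%/41.1% | 4.8 | 27% | 5% |
| 39%/39% | 5%/15% | 41.1%/45.9% | −4.8 | 27% | 5% |
| 49%/39% | 5%/15% | 51.6%/45.9% | 5.7 | 36% | 83% |
| 49%/39% | 15%/5% | 57.6%/41.1% | 16.6 | over 99% | 83% |

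For the 12%/8% row, completers number 426.5 × 0.88 = 375 and 426.5 × 0.92 = 392. The standard error is √(0.443·0.557/375 + 0.424·0.576/392) = 0.0358, and z = 0.0193/0.0358 = 0.54. Rejection is P(Z > 1.42) + P(Z < −2.50) = 0.084. The same formula at 15%/5% gives 0.27, in agreement with the simulation.

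**Power once leavers are coded no.** With 0.441 against 0.351 and 426.5 per arm, the null standard error is √(2·0.396·0.604/426.5) = 0.0335 and the alternative one is 0.0333. Then (0.090 − 1.96 × 0.0335)/0.0333 = 0.73, which is power of about 77%.

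**The case against.** **The outcome is not named as an imputed variable.** The sentence on MICE lists no variables. If leaving is a known no, nothing is missing and the rule never reaches link use; MICE would then serve only the likelihood score, the CSQ-3 and covariates. This reading is possible, and a reader who takes the article to say outright that the primary outcome is imputed goes beyond the text. The allowance for drop-out in the sample size points the other way, however, and nothing in the article states the benign coding.

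**Coding of leavers is detail for the full protocol or analysis plan.** That would answer a silence. Here a general rule is stated, and its plain application gives the worse result.

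**The outcome is defined after completion.** Its value for a non-completer is therefore arguably undefined, and link use had all completed is a coherent target. Leaving also does not prove that no help was sought. Both points are fair, but the article does not name that target, intention-to-treat points to the other one, and later contact is assigned to the likelihood proxy.

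**The 27% depends on chosen inputs.** This stands. No 15%/5% split appears in the article, and the scenario needs BRI completers to use the link more often by exactly enough to offset their extra drop-out. The base rate matters too. At an illustrative 10% in both arms, close to the proportion of test-takers (a different population) who go on to the contact page, the same split gives 11.8% against 10.5% and about 8% rejection.

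**The source of 0.49 and 0.39 is a cited study that is not at hand.** If those rates already count non-use as no among all randomised, there is no dilution and no loss of power. This stands as a condition on the 77%.

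**Conclusion.** The point holds as a defect of the rule as written: combined with intention-to-treat and drop-out before the link, it imputes a primary outcome whose value is known. It rests on reading the unrestricted sentence as covering link use, and on imputation by arm under missing at random.

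On the only drop-out figure that the article gives, taken as equal in both arms, the consequence is modest: 10.0 instead of 9.0 points and an odds ratio of 1.50 instead of 1.46. A reader might infer that imputation generally inflates the effect or invalidates the test. The documents do not support that. Under equal drop-out the risk ratio and the type I error are unaffected, and when more people leave the control arm, imputation shrinks the difference (from 10.0 to 5.7 points at 5%/15%).

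The serious consequence is conditional on unequal drop-out. False rejection then runs from about 8% at 12%/8% to about 27% at 15%/5% with true use of 39% in both arms. These splits are illustrations, not forecasts. Since the exposure concerns the primary test and is simple to remove, the rule should be changed before the data are analysed.

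**What to change.** In the Statistical Analysis section, state that for every randomised participant link use is yes if recorded and otherwise no, including anyone who leaves the session, and that link use is not imputed in the primary analysis. Restrict MICE to the likelihood score, the CSQ-3 and covariates. Report drop-out by arm. Present imputed or completer-only analyses of link use as sensitivity analyses. If the platform already codes leavers as no, say so.

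In the Sample Size section, say whether 0.49 and 0.39 are rates among completers or among all randomised. If they are completer rates, state that 853 randomised gives about 77% power instead of 80%, or recompute the number from 0.441 against 0.351.

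The cost is a few sentences and no new data collection. Under the completer reading, the price is three points of power or a somewhat larger sample.

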**Methods:**

People visiting the self-test for suicidal thoughts on the website of the suicide prevention helpline will be asked to participate in a study to improve the self-test. Individuals with severe suicidal thoughts and little motivation to contact the helpline will be randomly allocated either to a brief BRI, in which they will receive a short tailored message based on their self-reported barrier to the helpline (n=388) or care as usual (general advisory text, n=388). The primary outcome measure is the use of a direct link to contact the helpline after receiving the intervention or control condition. Secondary outcomes are the self-reported likelihood of contacting the helpline (on a 5-point scale) and satisfaction with the self-test. In the BRI, participants receive tailored information to address underlying concerns and misconceptions of barriers to the helpline. A pilot study was conducted among current test-takers to identify these specific barriers.

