### Procedure

After giving their informed consent and stating that they are 16 years or older, participants will be transferred from the helpline’s website to the Qualtrics platform. Figure 1 displays the study’s flowchart. During the screening phase, respondents start with the self-test. The self-test includes the SIDAS, which consists of 5 items on a 10-point scale measuring the frequency of suicidal thoughts, controllability, closeness to an attempt, distress, and interference with daily activities [17]. The self-test also contains questions regarding gender, age, and if the test-taker is currently in treatment for mental health problems. As mentioned in the exclusion criteria, if respondents score below the cutoff point for severe suicidal thoughts or score above the cutoff point but report that they are likely to contact the helpline, they will be excluded from the RCT.

After inclusion, participants will be randomly assigned to either the intervention or control condition. In both conditions, participants receive a barrier questionnaire to identify the reason why their self-reported likelihood of contacting the helpline in the screening phase was not very likely. After the barrier questionnaire, they receive a general advisory text (control) or an advisory text based on their selected barrier.

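### Free improvement: the primary test of link use is an unadjusted chi-square, although plausibly prognostic variables are already collected before randomisation; prespecified adjustment could add about 0 to 10 points of power

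*Protocol article*

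**What the plan says.** All references are to the protocol article.

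- **Primary test.** Statistical Analysis states: "Chi-square analysis will also be used to test the hypothesis that participants who receive the brief BRI are more motivated". The outcome is use of the direct link, yes or no, and no covariates are named. The same section assigns logistic regression to the questions about men, middle-aged people and potential moderators.
- **Sizing.** Sample Size states: "a sample size calculation for logistical regression analysis (2-tailed) indicates a total sample size of 775 participants". Its inputs are two probabilities ("When assuming probabilities of 0.49 and 0.39 for contacting the helpline for the intervention group and the control group, respectively"), and "a power of .8 and alpha of .05". No covariate effect is among them.
- **Baseline data.** Procedure and Measures list gender, age, SIDAS score and treatment status. Procedure also refers to the "self-reported likelihood of contacting the helpline in the screening phase", which is asked before randomisation. Under Exclusion Criteria, people who report being likely to make contact do not enter the trial.
- **Planned use of the baseline data.** Gender, age, SIDAS score and treatment status are to be tested between arms, and between completers and noncompleters: "In order to verify the randomization process and inspect drop-outs". Screening likelihood is not on that list.
- **Missing data.** The analysis is by intention to treat with MICE imputation, and about 10% dropout is expected.

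**The concern.** The screening question on likelihood of contact is the pre-randomisation counterpart of the trial's own proxy outcome. SIDAS score, gender, age group and treatment status could also plausibly relate to link use. A main comparison that leaves them out gives up whatever precision they offer, in a trial sized at 80% power with almost no margin.

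Three related points follow.

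1. Sample Size and Statistical Analysis name different methods for the main comparison.
2. With multiple imputation, a logistic coefficient or a risk difference pools directly by Rubin's rules. A chi-square statistic needs a special combining rule.
3. Significance tests between arms cannot verify randomisation. If allocation was random, any baseline difference is due to chance whatever the p-value. Such tests also add no precision to the main comparison.

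**Working it through.** **Inputs.** From Sample Size: p1 = 0.49, p0 = 0.39, two-sided alpha 0.05, power 0.80. From the abstract: 388 per arm. Normal quantiles are 1.960 and 0.8416. The prognostic strength of the covariates is not in the document and is assumed below.

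**Step 1: reproduce the plan's 775.**

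*Two proportions (chi-square, no continuity correction).* The mean rate is 0.44.

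n per arm = [1.960 × √(2 × 0.44 × 0.56) + 0.8416 × √(0.49 × 0.51 + 0.39 × 0.61)]² / 0.10²

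= [1.960 × 0.7020 + 0.8416 × 0.6984]² / 0.01 = 385.6, rounded up to 386, so 772 in total.

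*Logistic regression with arm as the only predictor (Wald).* The odds ratio is (0.49/0.51)/(0.39/0.61) = 1.503, and its log is 0.4073.

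n per arm = (1.960 + 0.8416)² × [1/(0.49 × 0.51) + 1/(0.39 × 0.61)] / 0.4073² = 388.2, so 776.4 in total.

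Two other logistic formulas give 771.2 (Hsieh) and 770.5 (variance-corrected Wald). The stated 775 therefore reproduces as a covariate-free logistic calculation, and the chi-square size of 772 differs from it by less than 1%.

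**Step 2: power of the planned test.** With 388 per arm:

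z = (0.10 × √388 − 1.960 × 0.7020) / 0.6984 = 0.850, which is 80.2% power.

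The two method names lead to the same trial size, so the mismatch costs nothing.

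**Step 3: power with adjustment.** The simulation used 388 per arm with marginal rates held at 0.49 and 0.39. One normally distributed score stood for the combined covariates. There were 3000 runs per row, with a Monte Carlo standard error of about 0.7 points. The adjusted test is the Wald test of the arm coefficient.

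| Assumed OR per SD of score | Chi-square | Unadjusted logistic | Adjusted logistic | Gain over chi-square (points) |
|---|---|---|---|---|
| 1.00 | 80.3% | 80.2% | 80.6% | 0.3 |
| 1.35 | 80.0% | 80.0% | 81.3% | 1.3 |
| 1.82 | 80.6% | 80.6% | 83.7% | 3.1 |
| 2.46 | 79.7% | 79.6% | 85.2% | 5.5 |
| 3.32 | 80.9% | 80.8% | 90.0% | 9.1 |

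Chi-square and unadjusted logistic regression agree to within 0.1 point. The gain comes from the covariates, not from the change of model.

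**Step 4: the gain as sample size.** The required size scales with (1.960 + z for power)². At 80% this is 7.85. At 81.3% it is (1.960 + 0.889)² = 8.12, and 7.85/8.12 = 0.97, or about 3% fewer participants for the same power. At 90.0% it is (1.960 + 1.2816)² = 10.51, and 7.85/10.51 = 0.75, or about 25% fewer.

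**The case against.** The strongest case against the point is that nothing here is an error. An unadjusted comparison of two proportions in a 1:1 randomised trial is unbiased and controls type I error, and it has the planned power. Adjustment is then an option. This stands, and it limits the point to efficiency and coherence.

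Several stronger readings are tempting but not supported:

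- *The trial is underpowered because it was sized for another method.* It is not. No covariate effect entered the calculation, and the sizes agree (Steps 1 and 2).
- *The covariates are strong predictors.* The document gives no such figure. Screening likelihood is truncated because likely contactors are excluded. The text does not say how many response levels remain, so its prognostic value may be modest.
- *Baseline variables serve only to compare the arms.* They are also used to compare completers with noncompleters, and gender and age enter the planned logistic models.
- *The baseline tests will drive the choice of adjustment.* The protocol plans no adjustment that depends on them.
- *No effect estimate will be reported, or the imputed data cannot be analysed.* Choosing a chi-square test does not rule out a risk difference with an interval, and combining rules for chi-square statistics exist. Such details are commonly left to an analysis plan, which is not shown here. They count as advantages of the alternative and are not omissions.

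The objections do not remove the case for adjustment. With uninformative covariates the simulated power was 80.6%, so nothing material is lost, and every variable needed is already collected.

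**Conclusion.** The point holds as a free improvement. The planned chi-square is valid and has about 80% power at 388 per arm. A prespecified adjusted logistic regression would have about 80% to 90% power if the combined covariate score has an odds ratio of 1.0 to 3.3 per SD, a gain of roughly 0 to 10 points. Where in that range the trial would fall cannot be read from the document, and the upper end needs strongly prognostic covariates.

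The figures rest on the protocol's assumed rates of 49% and 39%, on complete data for 388 per arm, and on one score standing for several covariates. The small cost of estimating several coefficients was not simulated.

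The differing method names should be aligned, but this is a matter of wording. The between-arm tests do not affect the primary inference; they simply cannot do what they are said to do.

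**What to change.** 1. Make the primary analysis a prespecified logistic regression of link use on arm, adjusted for screening likelihood of contact (the levels that remain after exclusion), SIDAS score, gender, age group and treatment status.
2. Fit it in each imputed data set and pool by Rubin's rules. Report the standardised risk difference with 95% CI, together with the odds ratio. The adjusted odds ratio is conditional on the covariates and differs in meaning from the crude one. The standardised risk difference targets the same quantity as the raw difference in link use.
3. State in advance which test decides the primary hypothesis, and keep the chi-square as a supportive unadjusted check.
4. Analyse the post-test likelihood of contact with its screening value as a covariate.
5. Replace the between-arm baseline significance tests with a descriptive table. The comparison of completers with noncompleters can stay.
6. Use the same method name in Sample Size and Statistical Analysis. The total of 775 need not change on this account.

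The cost is a change of wording before the data are analysed. No new data and no extra participants are needed.
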